**Methods/Design:**

The study is being conducted in a General Practice located in a deprived neighbourhood of Granada, Spain. Diabetic patients 18 years old or older with a low educational level and inadequate glycaemic control (HbA1c > 7%) were recruited. General Practitioners (GPs) were randomised to three groups: intervention A, intervention B and control group. GPs allocated to intervention groups A and B received training in communication skills and are providing graphic feedback about glycosylated haemoglobin levels. Patients whose GPs were allocated to group B are additionally receiving telephone reinforcement whereas patients from the control group are receiving usual care. The described interventions are being conducted during 7 consecutive medical visits which are scheduled every three months. The main outcome measure will be HbA1c; blood pressure, lipidemia, body mass index and waist circumference will be considered as secondary outcome measures. Statistical analysis to evaluate the effectiveness of the interventions will include multilevel regression analysis with three hierarchical levels: medical visit level, patient level and GP level.

**Discussion:**

The results of this study will provide new knowledge about possible strategies to promote a better diabetes self-management in a particularly vulnerable group. If effective, this low cost intervention will have the potential to be easily incorporated into routine clinical practice, contributing to decrease health inequalities in diabetic patients.

**Trial registration:**

Clinical Trials U.S. National Institutes of Health, NCT01849731.

## Background

It has recently been estimated that the prevalence of type 2 diabetes mellitus (T2DM) in Spain is 13.8% (adjusted by age and gender), and half of those patients did not know that they were diabetic [1]. Diabetes leads to significant microvascular and macrovascular complications, which imply a major financial burden on health services. In fact, it is estimated that a patient with T2DM uses 2 to 6 times more direct resources than people of the same age and gender with other chronic diseases [2]. However, diabetes does not affect all population groups equally; differences have been described according to socioeconomic status, ethnicity and gender, [3-5]. Thus, one systematic review showed that socioeconomic position inequalities affect T2DM incidence, prevalence and mortality in Europe, especially among women [6]. Similarly, a WHO-sponsored multinational study on vascular disease in T2DM [7] found that the mortality rate in people diagnosed with diabetes belonging to the lowest social group was double the rate of those in the highest group.

The scientific evidence shows that patients with a lower socioeconomic position have worse health literacy, and this in turn has been associated with inadequate self-management of diabetes. This has been attributed to a poor knowledge of the disease itself and to barriers in the verbal communication process within general practitioners and patients, which in turn influences beliefs and attitudes towards T2DM [4,8,9]. The increasing awareness of the impact of social inequalities on diabetes has led to the design, implementation and evaluation of healthcare interventions aimed at improving diabetes care in socially vulnerable population. These interventions, frequently also known as quality improvement strategies, are characterised by their variable nature, being based on direct actions with patients, conducted in primary care settings and targeted at specific ethnic groups or people of low socioeconomic status [10-12]. In general, the aim of these interventions is to increase knowledge of the disease, promote the use of health services and encourage behavioural changes related to disease self-care [10-12]. Thus, improvement in doctor-patient communication has been associated with better health outcomes [13], because patients understand their treatment, receive feedback from healthcare staff, and doctors are more collaborative [14].

Two systematic reviews of interventions to improve quality of diabetes care [11,15] identified an intervention that received attention because of its favourable results and its simplicity and feasibility to be incorporated in routine clinical practice. In this intervention Chapin et al. [14] developed a 1-page form to provide feedback to both patients and providers and tested it in an inner-city internal medicine clinic. The form was designed to facilitate providers’ documentation of patients’ self-care activities and glycosylated hemoglobin values in a format tailored to the clinic’s low-literacy population. The intervention involved placing the form with brief written instructions into patient charts. The study results showed that 51% of patients who received this intervention improved their HbA1c levels, while in the control group an improvement was only found in 18%, representing a statistically significant difference between the two groups.

As a result of an additional systematic review of strategies to improve quality of diabetes care in vulnerable population conducted by members of our team we have identified the provision of rapid turnaround of HbA1c availability as one of the most effective strategies to improve diabetes care [16].

In our country, despite the recognition of social inequalities, there is little experience on interventions among diabetic populations with a low socioeconomic status [10-12]. That is why we decided to carry out an intervention in primary care specifically aimed at improving the quality of diabetes self-management in people with low educational levels, adapting the intervention carried out by Chapin et al. [14].

This paper describes the study methods and presents data on the recruitment. The discussion highlights the recruitment challenges we encountered and the trade-offs between realistic field conditions and experimental control in the context of this effectiveness trial.

## Methods/Design

### Study design and aims

This study used a cluster randomized design. The protocol of this study is registered in the Clinical Trials U.S. National Institutes of Health database (Trial registration number: NCT01849731). The aim is to evaluate an intervention with two levels of intensity, versus usual care, among T2DM patients recruited from the general practice setting in a socially disadvantaged community. A cluster randomised design was used being General Practitioners (GPs) the unit of randomisation (cluster) and patients the unit of analysis. Cluster randomisation was used to control for potential contamination that could arise from having intervention and usual care patients allocated to the same GP [17]. GPs were randomised to provide one of the two interventions or usual care. We hypothesised that the more intense intervention (Intervention “B”) will have the greatest effect on diabetes-related health outcomes, the less intense intervention (Intervention “A”) will have an intermediate effect, and the usual care will have no appreciable effect (control group “C”).

### Study population and setting

The study was conducted in the Primary Care Centre “Cartuja” has the highest percentage of disadvantaged people in the city of Granada (Andalusia, Spain) [18]. A high proportion of patients attending to the centre is characterised by a low educational and income level and a high unemployment rate. The primary care centre is attended by 9 GPs and all were invited to participate in the study. Because the study is being conducted at a single health centre, we decided to include all adult patients (>18 years) with a diagnosis of T2DM who had a low educational level (illiteracy or primary school education) and inadequate glycaemic control (HbA1c > 7%). Patients were excluded if they were unlikely to complete the study, if their physical or mental condition would make study follow-up impossible, or if they were participating in another study. Withdrawal criteria were voluntary abandonment on the part of the patient and non-compliance with study requirements (not attending one of the scheduled visits in the intervention, refusal to provide blood samples or to complete the questionnaires).

We included all patients diagnosed with T2DM who met the inclusion criteria at each of the visits and attended the clinic between February and November 2011.

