#### Intervention A

(face-to-face intervention) is carried out by the GPs during the clinic visit and consists of seven visits, one every three months. Each session consists of completing a diabetes care record sheet (DCRS) together with the patient. The DCRS consists of two parts: Five questions on self-care activities in the last three months and a graph with previously measured HbA1c levels (see Figure 2). This information is completed at each session, resulting in a graph showing the evolution of glycaemic control related to self-care activities. The DCRS is explained patients, emphasising the relationship between self-care and glycemic control. At the end of the session, patients are given a copy of the DCRS and suggested to show it and discuss it with their relatives.

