### Evaluation of effectiveness

Intervention effectiveness will be measured as the proportion of patients who achieve adequate glycaemic control (HbA1c of less than 7%) by the end of the study.

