### Effectiveness assessment

Given the hierarchical structure of the information, the analyses will be performed using a multilevel model with three hierarchical levels: measurement (level 1), individual (level 2) and medical (level 3). The same levels of hierarchy will be used in the bivariate analyses, but adding a single independent variable to the model. All analyses will be carried out on an intention-to-treat basis.

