During the recruitment phase, one of the GPs did not arrange 14-day follow-up appointments for patients as stipulated in the study design. As a result, the baseline patient data used was from just 8 of the 9 GPs at the health centre. Although we considered replacing this GP, who declined to take part, with another similar one, in the end we could not do this for practical reasons.

Observed mean HbA1c value was 8.77%. For the control group this value was 8.57%, for intervention A it was 8.74% and for intervention B it was 9.16% (*p* = 0.031). For the lipid profile, the mean values of LDL, HDL and triglycerides were 122.82 mg/dL, 47.64 mg/dL and 208.91 mg/dL, respectively. There were no differences between the three groups. The mean systolic pressure was 130.63 mmHg (CG: 127.90; IA: 128.43 and IB: 137.16). The mean diastolic pressure was 74.47 mmHg (CG: 75.61; IA: 75.33 and IB: 78.94), with a significantly higher mean value in intervention group B. Likewise, significant differences were observed in the mean values of Body Mass Index, with 31.64, 34.47 and 33.25 kg/m2 being the mean values for the control group, intervention A and intervention B, respectively (*p* = 0.023).

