The main intervention was carried out by healthcare staff during patients’ usual appointments, so the participation rate was high. The intervention was also designed to be as simple as possible in order to minimise the amount of work required from the doctors taking part. However, although the intervention was well-received by medical staff, the recruitment process was slower than anticipated, so the recruitment phase was extended to 5 months so that enough patients could be recruited for each group. Furthermore, there were recruitment problems during the initial stages with one of the GPs, and no other reason for this was found apart from the usual workload pressure. This shows that in order for healthcare staff to be able to devote extra time to carrying out studies of this type, it would be a good idea to combine the research work with their normal patient appointments. Additionally, consultation of the patients’ computerised clinical histories revealed an estimated prevalence of diabetes of approximately 900 patients, an average of 100 patients per GP, enough for the desired sample group size. Although the GPs were randomised, the patients who met the inclusion criteria were not evenly distributed across the different GPs, especially in terms of their level of education. Finally, a large number of patients left the study between the first and second appointments.

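### Withdrawing patients for one missed visit or a refused questionnaire conflicts with intention to treat; if withdrawal ends measurement, end-of-study HbA1c is seen only in full attenders

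*Protocol article*

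**What the plan says.** All references are to the protocol article.

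- **Withdrawal.** *Study population and setting* names two grounds: the patient's own decision to leave, and "non-compliance with study requirements (not attending one of the scheduled visits in the intervention, refusal to provide blood samples or to complete the questionnaires"). One missed visit is enough.
- **Analysis set.** *Effectiveness assessment* states: "All analyses will be carried out on an intention-to-treat basis". The model is "a multilevel model with three hierarchical levels: measurement (level 1), individual (level 2) and medical (level 3").
- **Endpoint.** *Evaluation of effectiveness* uses "the proportion of patients who achieve adequate glycaemic control (HbA1c of less than 7%) by the end of the study".
- **Visit count.** *Intervention A* "consists of seven visits, one every three months", and the Abstract also gives seven. The *Control group* section gives five appointments over 15 months. It adds that eligible patients are already seen every three months for routine monitoring.
- **Losses already reported.** One GP did not arrange the 14-day appointments: "As a result, the baseline patient data used was from just 8 of the 9 GPs at the health centre" (*Trial status*). The *Discussion* adds that "a large number of patients left the study between the first and second appointments".

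**The concern.** Intention to treat needs an outcome, or a defensible treatment of its absence, for every patient in the arm as allocated. A rule that takes patients out of the study for non-attendance works against that, because it turns an intermittent gap into a permanent one.

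The gap is also not random. Keeping appointments is part of diabetes self-care, which is the behaviour the intervention aims to change and one that plausibly tracks HbA1c. The protocol would therefore itself produce missing outcomes related to adherence, in the comparison on which effectiveness is judged. A refused questionnaire is a weaker reason still, since it does not prevent HbA1c from being measured.

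**Working it through.** **Inputs.** Number of visits *v*: 7 (*Intervention A*, Abstract) or 5 (*Control group*). Attendance per visit *q*: not given in the documents, so assumed. Group sizes: 92, 37 and 52 (Table 1 headings). The article gives no figure for attendance or for expected withdrawal, so there is no plan figure to reproduce on this point.

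**Step 1. Share withdrawn under the rule.** With independent attendance and one common *q*, the share withdrawn is 1 − q^v.

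| Assumed q | v = 7 | v = 5 |
|---|---|---|
| 0.95 | 1 − 0.698 = 30% | 1 − 0.774 = 23% |
| 0.90 | 1 − 0.478 = 52% | 1 − 0.590 = 41% |

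In patients, if seven visits applied in every arm and *q* = 0.95, those never missing a visit would be about 92 × 0.698 = 64 control, 37 × 0.698 = 26 in A and 52 × 0.698 = 36 in B. At *q* = 0.90 they would be 44, 18 and 25.

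**Step 2. How much this depends on a common rate.** If patients differ in attendance, the mean of q^7 exceeds the seventh power of the mean, so fewer are withdrawn. Suppose half attend every visit and half attend with probability 0.90, giving a mean of 0.95. The share retained over seven visits is (1 + 0.478)/2 = 0.739, so 26% are withdrawn instead of 30%. Selection then becomes explicit: full attenders make up 0.5/0.739 = 68% of those retained, against 50% at entry.

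**Step 3. What the multilevel model can recover.** With measurement as level 1, HbA1c values up to withdrawal can enter the model in the allocated arm. Values after withdrawal cannot enter if they are never taken. The end-of-study proportion for those patients then rests on an assumption that their later HbA1c is predictable from their earlier HbA1c. That is doubtful when the reason for stopping is a lapse in self-care, and the data cannot test it once measurement has stopped.

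**Step 4. Whether the arms differ.** The seven-visit count describes the intervention. The five-appointment count stands under the control heading, but the surrounding text concerns scheduling of all study phases, interventions included, and *Study variables* gives one three-monthly measurement schedule for everyone. The two counts may be different schedules by arm or an inconsistency within one schedule. The rule's wording, which ties missed visits to the intervention, leaves it open whether controls are subject to it. No direction of bias follows until these places are reconciled.

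**Step 5. The other losses.** The ninth GP's patients dropped out of the baseline data because appointments were not arranged, not because of anything they did. Those who left before the second appointment are described as having left; the withdrawal rule is not given as the cause. Under *Procedure*, consenting patients completed a questionnaire and had blood drawn before the 14-day return, so some data on both groups may exist.

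**The case against.** The strongest reply is that withdrawal is nowhere equated with exclusion from the analysis. The article does not say that measurement stops or that earlier values are discarded, and the planned repeated-measures model can keep withdrawn patients in their allocated arm. The detail of the analysis set is commonly left to the full protocol or SAP. This stands as far as it goes: a reader might infer that the intention-to-treat analysis would in fact be an analysis of compliers, and the article does not support that as a statement of fact. It does not dispose of the point. The one-visit rule is stated here, and in its ordinary sense it ends collection of the very outcome that intention to treat requires.

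A reader might also infer that the rule filters A and B harder and so favours the intervention. That depends on reading seven and five as schedules that differ by arm, which the text does not establish.

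The attendance rates are assumptions, and a common independent rate tends to overstate the loss (step 2). Nothing in the article shows that 90% attendance, and hence withdrawal of about half the patients, should be expected.

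Lastly, the missing ninth GP and the early leavers might be taken as further evidence of selecting compliers. They are not. The first is a loss of a cluster through the GP's conduct, with neither the arm nor the timing relative to randomisation given. The second is attrition that the article discloses. The sentence about eight GPs also concerns baseline data and does not define the final analysis set.

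**Conclusion.** The point holds in conditional form. The withdrawal rule, the intention-to-treat promise and the end-of-study endpoint do not fit together as written. If withdrawal ends measurement, end-of-study HbA1c is observed only in patients who missed no visit, and the planned model corrects this only partly.

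Under assumed independent attendance of 90% to 95%, the share withdrawn is 30% to 52% with seven visits and 23% to 41% with five. These figures illustrate scale and are not forecasts. No direction of bias between arms is claimed. The ninth GP's patients and the early leavers are a separate matter of completeness: one of nine GPs (11%) contributes no baseline data.

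**What to change.** 1. Remove non-attendance and refused questionnaires as reasons to end study follow-up. Record them as missing values for that visit.
2. Keep collecting HbA1c from the routine three-monthly visits unless the patient withdraws consent.
3. Define the intention-to-treat set as all consenting patients in the arm to which their GP was randomised, and fit the multilevel model to all available HbA1c values.
4. Reconcile the seven visits and the five appointments, and state whether the schedule and the withdrawal criterion are the same in all arms.
5. Separately, report the ninth GP's arm and whether the loss came after randomisation. Include that GP's patients, and those lost before the second appointment, in the intention-to-treat set where consent and data allow.

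The cost is a change of wording, retrieval of HbA1c values from routine care, and somewhat more missing-data handling in the analysis.

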### Sample size

The power was calculated assuming that at the end of the intervention 10% of the control group and 30% of intervention groups A and B would achieve improved diabetes control (with HbA1c values falling to below 7%). In order to provide a level of confidence of 95%, a power to detect significant differences between groups A and B was 59.4%, while the power to detect differences between groups B and control was 57.9%.

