### Trial status: recruitment and baseline characteristics

Table 1 shows the results of the first (sociodemographic data) and second (clinical data) appointments. Whenever a patient who met the inclusion criteria (age 18 years, low education and inadequate glycemic control) came to visit, the GP asked if they would collaborate in the study. Of all, 16 of them decided not to participate.

**Table 1 T1:** Demographic and clinical characteristics of study subjects, by study group

		**All participants n =181 n (%)**	**Control group n = 92 n (%)**	**Intervention A n = 37 n (%)**	**Intervention B n = 52 n (%)**	**p**
Sex	Female	100 (54.3%)	44 (49.4%)	23 (63.9%)	31 (64.6%)	
	Male	80 (43.5%)	45 (50.6%)	13 (36.1%)	17 (35.4%)	0.143
Ethnicity	Caucasian	143 (80.8%)	77 (86.5%)	24 (66.7%)	36 (75%)	
	Romany/Other	34 (19.2%)	12 (13.5%)	12 (33.3%)	12 (25%)	0.033
Social support	High social support	44 (25.1%)	23 (25.6%)	2 (5.4%)	19 (39.6%)	
	Low social support	131 (74.9%)	67 (74.4%)	35 (94.6%)	29 (60.4%)	0.002
		**All participants Mean (SD)**	**Control group Mean (SD)**	**Intervention A Mean (SD)**	**Intervention B Mean (SD)**	**p**
Children		3.23 (2.16)	2.96 (3.33)	3.22 (3.69)	3.75 (2.16)	0.171
Age		61.66 (12.47)	62.37 (11.46)	60 (12.28)	61.59 (14.35)	0.721
HbA1c		8.77 (1.46)	8.57 (1.37)	8.74 (1.57)	9.16 (1.50)	0.031
Systolic pressure		130.63 (16.56)	127.90 (15.19)	128.43 (15.65)	137.16 (18.03)	0.004
Diastolic pressure		76.47 (11.32)	75.61 (9.41)	75.22 (11.04)	78.94 (14.18)	0.028
Abdominal circumference		107.44 (11.39)	105.73 (11.63)		111.16 (10.09)	0.030
HDL		47.64 (15.83)	48.66 (15.14)	46.43 (18.32)	46.64 (15.27)	0.378
LDL		122.82 (36.52)	125.40 (36.37)	120.64 (43.65)	119.56 (30.75)	0.453
Triglycerides		208.91 (165.13)	186.94 (89.40)	250.27 (258.79)	218.11 (179.53)	0.853
Body mass index		32.60 (5.72)	31.64 (5.40)	34.47 (5.50)	33.25 (6.17)	0.023

The sample is composed by a greater proportion of female patients (54.3%). The mean age of the sample is 61.99 years. Patients have an average of 3.23 children, and there are no significant between-group differences in these variables. Furthermore, 80.8% of the sample is Caucasian. A smaller proportion of this ethnicity is found in intervention group A (*p* = 0.033). Social support is low in the majority of the sample (74.9%), and the group B has a higher percentage of high social support (*p* = 0.002).

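### The two stated powers (59.4% for A versus B, 57.9% for B versus control) do not follow from the article's own rates and group sizes

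*Protocol article*

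**What the plan says.** The Sample size section of the protocol article computes power "assuming that at the end of the intervention 10% of the control group and 30% of intervention groups A and B would achieve improved diabetes"; the criterion for success is an HbA1c below 7%. The error rate is given only as "In order to provide a level of confidence of 95"%, without sidedness. Two powers follow: 59.4%, attached to the comparison of A with B, and the second, "while the power to detect differences between groups B and control was 57.9"%. The section gives no number per group, number of GPs, ICC, design effect, attrition allowance or test.

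Elsewhere the article supplies facts that bear on these figures:

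- Study design and aims: the trial is cluster randomised, "being General Practitioners (GPs) the unit of randomisation (cluster) and patients the unit of analysis". The stated hypothesis is ordered, with B expected to do best, A to be intermediate and usual care to show no appreciable effect.
- Trial status, Table 1: "Control group n = 92 n", with 37 in A and 52 in B.
- Trial status, text: "the baseline patient data used was from just 8 of the 9 GPs at the health centre". The split of those 8 by arm is not given.
- Effectiveness assessment: a "multilevel model with three hierarchical levels: measurement (level 1), individual (level 2) and medical (level 3").
- Discussion: an estimated sample size was hard to reach, but its value is not given. Many patients left between the first two appointments, again without a number.

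**The concern.** A stated power should be recoverable from the stated effect and the group sizes, with any further input named. Here the only effect is 10% versus 30% and the only group sizes are those in Table 1, and these do not give the printed figures. The first figure has a more basic problem: it is attached to two arms that are assumed to have the same success rate.

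Power is how a reader will judge a non-significant result in this trial. Since GPs were randomised, it depends on the number of GPs and the ICC as well as on patient numbers. If 57.9% came from a patient-level calculation on smaller groups, the real figure could be lower. If it already contains a cluster allowance, it may be about right. The reader cannot tell which. Nor can the reader tell whether the trial has any planned ability to separate A from B, which is what the secondary objective on telephone reinforcement needs.

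**Working it through.** **Inputs.** Rates 0.10 (control) and 0.30 (A and B), from Sample size. Recruited n of 92, 37 and 52, from Table 1. Two-sided 5% is assumed.

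**Formula.** Pooled two-proportion test: power = Φ((d − 1.96·SE0)/SE1). Here d = 0.20, SE0 = √[p̄(1−p̄)(1/n1+1/n2)], SE1 = √[0.10·0.90/n1 + 0.30·0.70/n2], and p̄ is the weighted mean rate.

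**1. A versus B as printed.** Both rates are 0.30, so d = 0. The probability of rejection is the type I error: 5% for the normal test, 3.8% for Fisher's exact test. It is not 59.4%.

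**2. B versus control, 52 versus 92.** p̄ = (9.2+15.6)/144 = 0.172; SE0 = 0.0655; SE1 = 0.0708. Power = Φ((0.20−0.1284)/0.0708) = Φ(1.01) = **84.4%**. Other two-sided versions on the same numbers:

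| Version | Power |
|---|---|
| Unpooled | 80.6% |
| Pooled, continuity correction | 78.8% |
| Unpooled, continuity correction | 74.3% |
| Fisher exact | 83.4% |
| Arcsine | 84.4% |

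Using the slightly smaller item denominators in Table 1 (89 or 90 versus 48) gives 71% to 83%. None comes near 57.9%.

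**3. A versus control, 37 versus 92** (if this is what 59.4% was meant to describe). p̄ = (9.2+11.1)/129 = 0.157; SE0 = 0.0709; SE1 = 0.0816. Power = Φ(0.75) = **77.3%**.

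**4. What would give 57.9% for B versus control?** Each of these needs an input that the article does not state:

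| Added input | Power |
|---|---|
| 37 per arm, no clustering | 57.8% |
| 50% loss (46 versus 26), no clustering | 57.3% |
| 52 versus 92, ICC 0.041, 3 GPs per arm | 57.9% |
| 52 versus 92, ICC 0.05, one design effect with m = 181/9 = 20.1 | 58.2% |

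For the third row, the design effect is 1+(m−1)·ICC. Control has m = 92/3 = 30.7, so the design effect is 2.23 and effective n is 41.3. B has m = 52/3 = 17.3, so the design effect is 1.68 and effective n is 31.0. Power is Φ(0.20) = 57.9%.

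**5. Can one input explain both figures, reading 59.4% as A versus control?** Five splits of GPs over the arms were tried. Setting the ICC so that B has 57.9% gives A between about 52% and 57%. A uniform 50% loss gives 57.3% for B and 51.2% for A. Patient-level arms of 37 and 38 give 57.8% and 59.0%, which is close to both printed figures but not exact.

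**6. Illustration with clustering.** Assume 3 GPs in B and 3 in control, with the recruited sizes.

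| ICC (assumed) | Design effect, control / B | Effective n, control / B | Normal approximation | t, 5 df | t, 4 df |
|---|---|---|---|---|---|
| 0.01 | 1.30 / 1.16 | 71.0 / 44.7 | 77% | 55% | 50% |
| 0.05 | 2.48 / 1.82 | 37.0 / 28.6 | 54% | 38% | 34% |
| 0.10 | 3.97 / 2.63 | 23.2 / 19.7 | 38% | 27% | 25% |

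The t columns use a noncentral t with unpooled variance. The 5 df are 8 GPs minus 3 arms; the 4 df are 3+3 GPs minus 2.

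**The case against.** The article never says that its powers use the recruited numbers, and a full protocol may hold the sample sizes and cluster allowance. It is also candid: both figures are below 60%, and the Discussion concedes limited power. All of this stands, and it is why 57.9% is best called untraceable rather than proven wrong. It does not rescue 59.4%. No sample size, ICC or attrition rate creates power between two arms assumed equal.

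Four stronger readings are tempting, and the article does not support them.

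- *Clustering was ignored.* Equal arms of 37 to 38 come close to both figures, which makes this plausible. But no such planning size appears in the article, and 57.9% for B versus control fits equally well with an ICC near 0.04 on the recruited numbers, or with about half the patients lost.
- *The figures are in an impossible order, because A is smaller than B.* This first requires reading 59.4% as A versus control, which is not what is printed. It also fails under clustering: with 3, 3 and 2 GPs in control, A and B and an ICC of 0.05, power against control is 51.0% for A and 50.7% for B.
- *The power of the main comparison is affected.* The article names no comparison as the main one; it states an ordered hypothesis over three arms.
- *The planned analysis will be too liberal with 8 GPs.* The Effectiveness assessment section includes the GP level and does not specify a Wald z test. The degrees-of-freedom method is commonly left to the SAP, which is not shown.

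**Conclusion.** The point holds as a defect in the power statement. The 59.4% is wrong as labelled, and this needs no assumption beyond the article's own 30% in both arms. The 57.9% does not follow from the stated rates and recruited sizes: patient-level power is 84% (74% to 84% across two-sided methods on 52 versus 92). It needs an unstated group size, attrition rate or ICC. If 59.4% was meant for A versus control, the patient-level figure is 77%.

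Which input was used cannot be settled from the article, so neither neglect of clustering nor a correct allowance for it can be claimed. The clustered figures rest on an assumed ICC and an assumed 3 GPs per compared arm. They show how far the answer moves (77% to 38% by normal approximation, lower with a t reference) and are not a corrected power for the trial.

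**What to change.** - Correct the comparison attached to 59.4%.
- Restate power for A versus control and for B versus control from the recruited sizes (37 versus 92 and 52 versus 92) and the 8 contributing GPs. Give n, GPs per arm, the attrition allowance, the test and its sidedness, and a range of ICCs.
- If A versus B is to be tested, state a non-zero assumed difference that agrees with the ordered hypothesis in Study design and aims. Otherwise say that the trial is not powered for that comparison.
- As a recommendation only, not to correct an error: with 8 GPs, use small-sample degrees of freedom (Kenward-Roger or Satterthwaite) for the arm effects in the multilevel model. The cost is wider intervals, up to about 30% (t on 5 df, 2.57 against 1.96).

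Recruitment is complete, so none of this changes the design. The cost is a few rewritten lines and a figure that will probably look less favourable than the printed one.
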